**Baseline**					
Sex (male/female) Side of hemiplegia (left/right)	**√**				
Type of stroke (ischemia/hemorrhage)	**√**				
Age, y BMI	**√√**				
Time since stroke, y **Primary outcome variable FMA-UE(66)**	**√**				
A. Upper Extremity (36)	**√**	**√**	**√**	**√**	**√**
B. Wrist (10)	**√**	**√**	**√**	**√**	**√**
C. Hand (14)	**√**	**√**	**√**	**√**	**√**
D. Coordination/Speed (6)	**√**	**√**	**√**	**√**	**√**
**Secondary outcome variables**	**√**	**√**	**√**	**√**	**√**
**MMT**	**√**	**√**	**√**	**√**	**√**
**Ashworth Scale EEG**	**√√**	**√√**	**√√**	**√√**	**√√**
**Lindmark Motor Score**	**√**	**√**	**√**	**√**	**√**
**Barthel Index**	**√**	**√**	**√**	**√**	**√**

“√” indicates that the variable is assessed at the corresponding timepoint.

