### Study sample

Based on a preliminary RCT (23) investigating TENS for post-stroke upper-limb motor rehabilitation, the sample size was derived using a moderate standardized effect size (*d* = 0.5) on the primary endpoint (FMA-UE), two-sided α = 0.05, and power (1–β) = 0.80. The required sample is 128 participants (32 per group). Allowing for ~20% attrition, the target enrollment is 156 (39 per group).

A total of 156 participants will be recruited from the Rehabilitation Department of Shenzhen Bao'an District Fuyong People's Hospital. Inclusion criteria are: (1) age 40–80 years; (2) clinically confirmed ischemic or hemorrhagic stroke 10 days to 2 months prior to enrollment; (3) Brunnstrom stage III–V for upper-limb motor recovery (mild to moderate impairment); (4) baseline FMA-UE 15–55; (5) able to perform ≥ Grade 2 voluntary movement (gravity-eliminated) in the paretic upper limb on MMT.

Exclusion criteria include: (1) any uncontrolled or unstable medical, cardiovascular, neurological, or orthopedic condition that could interfere with rehabilitation or study participation; (2) contraindications to TENS (e.g., implanted pacemaker, metal near the stimulation site, active skin lesions, known electrode allergy); (3) severe receptive aphasia, MoCA < 20 indicating moderate–severe cognitive impairment, or any psychiatric illness that could interfere with understanding instructions or providing informed consent; (4) clinically significant peripheral neuropathy of the paretic upper limb, diagnosed clinically or via electrophysiology; (5) concurrent participation in another interventional clinical trial or use of investigational drugs; (6) severe contractures/deformities or fixed joint limitations of the shoulder, elbow, wrist, or fingers that preclude voluntary movement or electrode placement; (7) Brunnstrom stage I–II of the upper limb.

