### Statistical analysis

All analyses will be performed in SPSS 27.0 on the intention-to-treat set. Baseline characteristics will be compared with one-way ANOVA or Kruskal–Wallis tests (continuous) and chi-square or Fisher's exact tests (categorical). The primary endpoint is FMA-UE; the primary comparison is 100 Hz vs. 2 Hz at week 8. Longitudinal changes will be analyzed using a linear mixed-effects model with random intercepts (participants), fixed factors group (2 Hz, 100 Hz, placebo, control) and time (baseline, week 4, week 8, 1 month post-discharge, 3 months post-discharge), and the group × time interaction; prespecified covariates (age, sex, time since stroke, stroke type, side of hemiplegia) will be included. Other pairwise contrasts will be adjusted using the Holm method; Brunnstrom-stage subgroup analyses will be exploratory via interaction terms. Secondary continuous outcomes will use the same LMM; ordinal outcomes (MMT, MAS, Lindmark) will use proportional-odds mixed models. Missing data will not use LOCF; inference will rely on the LMM under MAR with multiple-imputation sensitivity.

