### Analysis

The primary outcome will be the change in FMA–UE from baseline to week 4, week 8, 1 month post-discharge, and 3 months post-discharge. The primary contrast will be 100 Hz vs. 2 Hz at week 8; other time-point contrasts will be supportive/exploratory.

A prespecified subgroup analysis by Brunnstrom stage (III/IV/V) will examine whether frequency effects differ by motor-recovery stage (exploratory interpretation). Within the FMA–UE, we will also explore segment/domain effects (proximal vs, distal components and the coordination/speed subscale).

Secondary outcomes will include MMT (wrist flexor/extensor strength), MAS (wrist-flexor spasticity), Lindmark Motor Score—hand subscale (grasp), and the Barthel Index (ADLs). These measures complement the FMA–UE by capturing muscle strength, spasticity, hand function, and functional independence.

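### As written, the primary mixed model's adjustment for time since stroke cancels from the week-8 change contrast; the cost is precision, not bias

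*Protocol article*

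**What the plan says.** All references are to the protocol article.

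- **Model (Statistical analysis).** A linear mixed model for FMA-UE with a random intercept per participant, four groups and five levels of time, of which baseline is one, "and the group × time interaction". On covariates it says only that "prespecified covariates (age, sex, time since stroke, stroke type, side of hemiplegia) will be included". No covariate × time term is named.
- **Contrast.** Statistical analysis says that "the primary comparison is 100 Hz vs. 2 Hz at week 8", without saying whether this is a level or a change. The later Analysis section settles it as a change: "The primary outcome will be the change in FMA–UE from baseline to week 4, week 8", with the same two arms compared at week 8.
- **Population (Study sample).** Patients must have a "clinically confirmed ischemic or hemorrhagic stroke 10 days to 2 months prior to enrollment".
- **Stratification (Randomization).** Brunnstrom stage, sex, stroke type and lesion side. Time since stroke is not a factor.
- **Recording (Table 1).** The row label is "Time since stroke, y", that is, years.

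**The concern.** The entry window runs from 10 days to about two months after stroke, roughly a six-fold range. The article itself treats spontaneous recovery as a competing explanation for improvement (Discussion) and expects it to level off only later (Follow-up timepoints and assessment procedures). How much a patient gains over eight weeks may therefore depend on how early that patient entered. The plan lists time since stroke as a covariate, presumably to deal with this.

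A time-constant main effect cannot do so for a change from baseline when baseline is itself one of the modelled responses. A reader of the plan, and later of the results, would take the primary contrast as adjusted for time since stroke when in effect it is not. What is at stake is the precision that the adjustment was meant to buy, and the correction of any chance difference in time since stroke between the two active arms.

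**Working it through.** The plan gives no figure for this adjustment, so there is none to reproduce. The check is algebra, then a simulation, then a range for the size.

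**1. Algebra.** For participant i in arm g at visit j, with time since stroke t:

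E(Y) = μ + α_g + τ_j + (ατ)_gj + β·t_i

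The expected change to week 8 is (τ_8 − τ_0) + (ατ)_g8 − (ατ)_g0 + β·t_i − β·t_i. The last two terms cancel, so β appears neither in the change nor in the difference in change between arms. With a visit-specific slope β_j, the change contains (β_8 − β_0)·t_i, and the covariate then acts on the contrast.

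**2. Simulation.** Four arms of 32 (the article's evaluable number per group), five visits and a random-intercept model. Assumed, not from the documents: t uniform on 10 to 61 days; baseline mean rising 0.1 point per day of t; mean 8-week gain 10 − 0.2·(t − 35) points; SDs of 8 (participant), 4 (gain) and 3 (residual). Results for two of the arms in one complete data set:

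| Time since stroke in the model | Week-8 change contrast (SE) | Week-8 level contrast |
|---|---|---|
| Absent | −0.029143 (1.374338) | −0.222 |
| Main effect, days | −0.029143 (1.374338) | −0.111 |
| Main effect, years (unrounded) | −0.029143 (1.374338) | −0.111 |
| × visit, days | 0.315 (1.282) | −0.046 |
| × visit, years (unrounded) | 0.315 (1.282) | −0.046 |
| × visit, years to one decimal | 0.709 (1.321) | 0.366 |

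The main effect leaves the change contrast untouched but moves the level contrast.

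Over 80 simulated trials with 20% dropout, the main effect moved the change contrast by 0.009 points on average (maximum 0.045). The interaction moved it by 0.65 on average (maximum 3.1). The empirical SD of the contrast was 1.55 without the covariate, 1.55 with the main effect and 1.41 with the interaction.

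**3. Size as a general range.** Let ρ be the absolute correlation of time since stroke with week-8 change. The documents do not give it, so it is an assumption.

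- SE multiplier when the covariate acts on the change: √(1 − ρ²).
- Shift in the contrast from a one-standard-error chance imbalance at 32 per arm, in SDs of change: ρ·√(2/32) = 0.25ρ. With t uniform on 10 to 61 days, the SD is 51/√12 = 14.7 days, and one standard error of imbalance is 14.7 × √(2/32) = 3.7 days.
- Power of a two-sided t-test at 32 per arm, with d = 0.5 taken in SDs of change. It is 0.50 unadjusted; that this falls short of the planned 0.80 is a separate matter.

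| ρ | SE multiplier | One-SE shift (SD of change) | Power, adjusted |
|---|---|---|---|
| 0.2 | 0.98 | 0.050 | 0.52 |
| 0.3 | 0.95 | 0.075 | 0.54 |
| 0.4 | 0.92 | 0.100 | 0.57 |
| 0.5 | 0.87 | 0.125 | 0.62 |

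The simulation sits near the upper end of this range. The part of the gain due to t has SD 0.2 × 14.7 = 2.94, and the change has SD √(2.94² + 4² + 2 × 3²) = 6.5, so ρ is about 0.45. The predicted multiplier is √(1 − 0.45²) = 0.89; the simulated one is 1.41/1.55 = 0.91.

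**4. Unit.** 10/365.25 = 0.027 and 61/365.25 = 0.167 years. Unrounded years and days give identical contrasts in every model. In whole years every eligible patient is 0. To one decimal only 0.0, 0.1 and 0.2 remain, and the interaction model's SE is then 1.321 instead of 1.282.

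**The case against.** The strongest reply is that the article neither states nor excludes covariate × time terms. It condenses a fuller document, and the analysis plan, which is not shown, may settle how covariates enter. This stands as a limit: main effect only is the natural reading of a model that names one interaction and then lists covariates, but it is a reading. It does not remove the point, because the terms the article does state do not deliver the adjustment that the list implies.

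Second, the Statistical analysis section taken alone can mean a week-8 level difference, and the main effect does adjust that. This also stands, but the Analysis section says change. Even on the level reading, one coefficient is pooled over baseline and all later visits, and it fits week 8 poorly if the association changes as patients recover. That costs efficiency, not validity.

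Three stronger readings are tempting, and the documents do not support them:

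- **That the primary comparison is biased.** Allocation is randomised, so an imbalance in time since stroke is chance error already carried by the standard error.
- **That recording in years disables the adjustment.** Rescaling a covariate changes no contrast, and the article states no rounding rule.
- **That nothing else reflects recovery position.** Brunnstrom stage is the article's own recovery staging and is a stratification factor. Baseline FMA-UE is limited to 15–55 by eligibility and enters the model as a response. Neither is in the covariate list, but both limit how far the arms can differ.

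**Conclusion.** The point holds on the natural reading of the model together with the Analysis section's definition of the primary outcome. The main effect of time since stroke then drops out of the week-8 change contrast, exactly with complete data and almost exactly with 20% dropout. The cancellation needs no assumption about recovery.

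The size does rest on an assumption, namely ρ. For ρ from 0.2 to 0.5 the forgone reduction in SE is about 2% to 13%. A one-SE chance imbalance left uncorrected amounts to 0.05 to 0.125 SD of change, which is 10% to 25% of the planned d = 0.5. If ρ is low, little is lost. This is a modest loss of efficiency and a mismatch between what the plan appears to adjust for and what it does adjust for. It is not a threat to validity. The Table 1 unit is a separate labelling matter that carries a rounding risk.

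**What to change.** 1. In the primary mixed model, enter time since stroke with its interaction with visit. Alternatively, model week-8 FMA-UE with baseline FMA-UE and time since stroke as covariates; once baseline is a covariate, the arm contrast is the same for the week-8 level and for the change.
2. State once, in the same words in both sections, that the primary week-8 contrast is a change from baseline.
3. Correct the unit in Table 1 from years to days, so that rounding cannot erase the variable.

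Cost: four extra degrees of freedom, a slightly longer model and one unit on the case report form, with no additional patients or visits. The gain is small if time since stroke turns out to be only weakly related to change. The amendment should be made before unblinding.

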**Figure 1 F1:**
[figure not shown]
Anticipated CONSORT flow diagram for participant recruitment and allocation.

The primary outcome is the FMA-UE, which evaluates motor control from proximal to distal segments and the transition from synergistic to isolated movements in stroke survivors (15). The FMA-UE has demonstrated excellent inter-rater (ICC = 0.997) and intra-rater reliability (ICC = 0.993) (16).

Secondary outcomes include:

Muscle strength of wrist flexion and extension, assessed by MMT, rated on a scale from 0 (no contraction) to 5 (normal strength). MMT has shown strong inter-rater reliability when performed by trained evaluators across various conditions (17).Spasticity of the wrist flexors, measured using the Modified Ashworth Scale, which exhibits good intra-rater reliability in patients with upper limb hemiparesis (18).Hand grasp function, evaluated using a subscale of the Lindmark Motor Score, a valid and reliable measure of hand motor function (19).Functional independence, assessed by the Barthel Index, which evaluates performance in basic activities of daily living and is widely used in stroke research and clinical practice (20).Cortical excitability and interhemispheric balance, measured using resting-state EEG. EEG signals will be recorded with standard 10–20 electrode placement, focusing on α (8–13 Hz) and β (13–30 Hz) band power at C3 and C4 electrodes. The α/β power ratio between C3 and C4 will be computed to assess hemispheric balance. These EEG markers have been widely used to reflect motor cortex activation and neuroplasticity changes following neuromodulatory interventions in stroke patients (21, 22).

Covariates include age, sex, body mass index (BMI), time since stroke onset, type of stroke (ischemic or hemorrhagic), and side of hemiplegia (left or right). Outcome assessors and the statistician will be blinded to group allocation. A detailed timeline and classification of outcome measures are provided in Table 1.

**Table 1 T1:** Schedule of assessments and outcome measures across study timepoints.

	**Before-intervention**	**Mid-intervention**	**Post-intervention**	**1-mo follow-up**	**3-mo follow-up**
**Time (Months)**	**0**	**1**	**2**	**3**	**5**

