### Randomization

After written informed consent and baseline assessments, participants will be randomized by an off-site research assistant using a computer-generated sequence in SPSS (fixed permuted blocks of 8) in a 1:1:1:1 ratio to 2 Hz TENS, 100 Hz TENS, placebo TENS, or a no-TENS usual-care control. Allocation concealment will be ensured with sequentially numbered, opaque, sealed envelopes prepared by personnel independent of enrollment and assessment. Stratified block randomization will be used by Brunnstrom stage (III/IV/V), sex (male/female), stroke type (ischemic/hemorrhagic), and lesion side (left/right). Outcome assessors will remain blinded to group assignment.

To support participant blinding between active and sham arms, the placebo TENS device will be identical in appearance and procedures, will deliver a brief ramp-up to a just-perceptible tingling (~20–30 s), and will then fade to an imperceptible output while maintaining visual cues. Participants in the no-TENS control arm will not be blinded; TENS operators cannot be blinded due to device setup and will not perform outcome assessments. Electrode placement will follow a predefined protocol by Brunnstrom stage (e.g., wrist extensors in stage III; finger extensors/supinators in stage IV; intrinsic hand muscles in stage V). All operators will receive standardized training to ensure consistent application.

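### Brunnstrom stage is the only stratification factor left out of the primary mixed model, which costs precision and makes the test conservative but does not bias 100 Hz vs 2 Hz

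*Protocol article*

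**What the plan says.** Randomization section: "Stratified block randomization will be used by Brunnstrom stage (III/IV/V), sex (male/female), stroke type (ischemic/hemorrhagic), and lesion side (left/right", with "fixed permuted blocks of 8".

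Statistical analysis section: the primary model is a "linear mixed-effects model with random intercepts (participants), fixed factors group (2 Hz, 100 Hz, placebo, control) and time", plus the group × time interaction, and "prespecified covariates (age, sex, time since stroke, stroke type, side of hemiplegia) will be included". Side of hemiplegia stands in for lesion side, so sex, stroke type and side are covered. Stage is mentioned once more in that section: "Brunnstrom-stage subgroup analyses will be exploratory via interaction terms". The later Analysis section repeats the stage subgroup analysis as exploratory.

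The covariate paragraph before Table 1 gives a second list: "Covariates include age, sex, body mass index (BMI), time since stroke onset, type of stroke (ischemic or hemorrhagic), and side of hemiplegia". It contains BMI; the list in the Statistical analysis section does not. Neither list contains stage, and neither difference is explained.

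**The concern.** A factor used to stratify randomisation normally belongs in the primary model. Stratification makes the arms more alike on that factor, so the treatment contrast varies less from trial to trial. A model without the factor leaves its variance in the error term, and the reported standard error then overstates the true one. If the factor predicts the outcome, the price is wasted precision and a test whose real type I error lies below 5%.

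The omission is a stated choice and not a detail left to an unseen analysis plan: the article gives a closed list, and that list does not match its own stratification. A link between stage and FMA-UE is plausible from the protocol's own descriptions, since both are placed on the path from synergistic to isolated movement. At stake is the efficiency of the week-8 comparison of 100 Hz with 2 Hz, in a trial with little precision to spare.

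**Working it through.** **1. Factors against model terms.**

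| Stratification factor | In primary model? |
|---|---|
| Brunnstrom stage (III/IV/V) | No; exploratory interaction only |
| Sex | Yes |
| Stroke type | Yes |
| Lesion side | Yes, as side of hemiplegia |

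**2. Inputs.** From the Study sample section: d = 0.5, two-sided α = 0.05, power 0.80, 32 evaluable per group (128 in total), 156 enrolled. From the Randomization section: 3 × 2 × 2 × 2 = 24 strata and blocks of 8. The share of outcome variance explained by stage (R²) is not in the documents; 0.1 to 0.5 is assumed.

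**3. The plan's own figure.** The article gives no figure for the effect of stage. Its one computed figure is the sample size. With d = 0.5 the usual formula needs 63 (normal) or 64 (t-test) per arm, so 128 reproduces as a two-arm total, and 32 per group does not. At 32 per group, power for 100 Hz vs 2 Hz is 0.52 (normal) or 0.50 (t-test). That is a separate matter; it is used here only as the starting point for step 5.

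**4. Week 8 compared as a level: standard error.** The ratio of reported standard errors without and with stage is 1/√(1 − R²):

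- R² = 0.1: 1/√0.9 = 1.05
- R² = 0.3: 1/√0.7 = 1.20
- R² = 0.5: 1/√0.5 = 1.41

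**5. Week 8 compared as a level: power and type I error.** By formula, multiplying the SD by √(1 − R²) raises power at 32 per arm from 0.52 to 0.56, 0.67 and 0.81. A simulation gives the operating characteristics (4000 runs per setting, N = 128, four arms, 24 strata, blocks of 8, a linear model at a single timepoint; Monte Carlo standard error near 5% is √(0.05 × 0.95/4000) ≈ 0.003):

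| R² | Type I, stage omitted | Type I, stage included | Power, omitted | Power, included |
|---|---|---|---|---|
| 0.1 | 0.037 | 0.043 | 0.52 | 0.55 |
| 0.3 | 0.032 | 0.058 | 0.50 | 0.65 |
| 0.5 | 0.019 | 0.051 | 0.50 | 0.79 |

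With stage omitted, type I error falls below 5% and power stays near one half. With stage included, type I error scatters around 5%.

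**6. Week 8 compared as change from baseline.** The model keeps baseline as a time level with a random intercept per participant. The group × time contrast at week 8 is then a difference of within-participant changes, and a stage effect that is constant over time cancels. Fits of this structure to simulated data (32 per arm, 5 visits, strong stage effect on level, one data set per setting, other covariates left out) show this:

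- Complete data, stage main effect added: SE 0.212 with and without stage.
- About 20% dropout, stage main effect added: SE 0.243 to 0.2425.
- Stage also driving the slope, stage × time added: SE 0.226 to 0.211, a ratio of 0.226/0.211 = 1.07.

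These are single data sets and show order of magnitude only.

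**7. Balance.** 156/24 = 6.5 participants per stratum on average, against a block of 8. Many blocks will be incomplete, so balance on stage is not guaranteed. Adjustment would also cover any residual imbalance.

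**The case against.** The strongest reply is that the primary outcome in the Analysis section is change in FMA-UE from baseline, so the model already absorbs most of what stage explains, and the 5% to 41% range describes a contrast the trial may not use. This stands in part. The Statistical analysis section names FMA-UE at week 8 as the comparison, with no baseline covariate, while the Analysis section speaks of change. The range must therefore be tied to the level reading, and the loss called small under the change reading.

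It is also fair that no threat to validity has been shown. Randomisation is stratified on stage, omission lowered type I error in the simulation, and nothing favours either frequency.

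A reader might infer more than the documents support:

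- **That stage is documented as the most prognostic factor.** It is not. Relevance to FMA-UE is a reasonable inference, but no ranking or R² is given.
- **That electrode site is a reason to adjust.** "Electrode placement will follow a predefined protocol by Brunnstrom stage", and the rule is the same in both active arms, so site cannot confound 100 Hz vs 2 Hz. At most it suggests effect modification, which the exploratory interactions address.
- **That the ordinal models are stated to lack stage.** The article lists no covariates specifically for them.
- **That the Table 1 entry "Time since stroke, y" loses information.** A change of unit only rescales a coefficient. Loss would need coarse rounding, which is not stated anywhere.
- **That the BMI mismatch leaves the primary model open.** The Statistical analysis section is the natural governing text, so this is an inconsistency to tidy.

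**Conclusion.** The point holds as one of efficiency and internal consistency. Stage is the one stratification factor absent from the primary model, and the exploratory interactions do not put it there. The consequence is a conservative test and lost precision, with no bias in the primary contrast.

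The loss is potentially substantial under the level reading, and the range in step 4 rests wholly on the assumed R². Under the change reading a main effect of stage adds almost nothing, and stage × time helps modestly, if stage affects the rate of recovery. The simulation in step 5 uses one timepoint without baseline information, so it is an upper guide. Adjustment should not be seen as a remedy for the sample size: on the formula in step 5 it reaches 0.80 power only if stage explains about half of the outcome variance and week 8 is compared as a level.

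**What to change.** Add Brunnstrom stage (III/IV/V) and stage × time as fixed effects in the primary mixed model and in the mixed models for continuous secondary outcomes. Having both terms serves either reading of the week-8 contrast. The cost in the model is 2 parameters for stage and 2 × 4 = 8 for stage × time over the five visits. Include stage in the proportional-odds models when their covariates are specified. Keep the stage subgroup analyses exploratory.

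As a minor tidy-up, make the covariate paragraph before Table 1 and the Statistical analysis section agree on BMI, either by adding it to the model or by describing it only as a baseline characteristic.

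Stage is already recorded for stratification, so nothing new is collected. The change is wording, to be made before unblinding.
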